## Abstract

**Background:**

Cancer-related fatigue (CRF) and its impact on patients' quality of life has been an increasing subject of research. However, in Germany there is a lack of evidence-based interventions consistent with the multidimensional character of fatigue. The objective of this study is to develop and evaluate a self-management program for disease-free cancer patients to cope with CRF.

**Methods:**

Based on evidence extracted from a literature review, a curriculum for the self-management program was elaborated. The curriculum was reviewed and validated by an interdisciplinary expert group and the training-modules will be pretested with a small number of participants and discussed in terms of feasibility and acceptance.

To determine the efficacy of the program a randomised controlled trial will be carried out: 300 patients will be recruited from oncological practices in Bremen, Germany, and will be allocated to intervention or control group. The intervention group participates in the program, whereas the control group receives standard care and the opportunity to take part in the program after the end of the follow-up (waiting control group). Primary outcome measure is the level of fatigue, secondary outcome measures are quality of life, depression, anxiety, self-efficacy and physical activity. Data will be collected before randomisation, after intervention, and after a follow-up of 6 months.

**Discussion:**

Because there are no comparable self-management programs for cancer survivors with fatigue, the development of the curriculum has been complex; therefore, the critical appraisal by the experts was an important step to validate the program and their contributions have been integrated into the curriculum. The experts appreciated the program as filling a gap in outpatient cancer care.

If the results of the evaluation prove to be satisfactory, the outpatient care of cancer patients can be broadened and supplemented.

**Trial Registration:**

ClinicalTrials NCT00552552

## Background

Most cancer patients experience fatigue as a symptom of their disease or as a side effect of treatment with chemotherapy, radiation therapy, immunotherapy or surgery. It is described as a subjective feeling of extreme tiredness and decreased functional status, which are not adequate to activities performed and are not relieved by sleep or rest [1]. The specific manifestations may be physical, mental or emotional [2].

A small number of patients recover from cancer-related fatigue after cessation of treatment, but in a significant proportion of cancer survivors the fatigue persists for several months or even years. Estimated rates for the prevalence of fatigue in disease-free cancer patients range from 17% to 56% subject to type and stage of cancer and the fatigue assessment instrument [3-7]. But often CRF is not diagnosed because cancer survivors rarely report it and doctors and nurses do not automatically focus on this symptom [1,8].

CRF is described as a more distressing symptom than nausea, vomiting or pain and it impairs the quality of life [8-12]. According to this, everyday life is also severely restricted: it leads to prolonged disability with consequences for the resumption of social life as well as work [13-15].

The aetiology of CRF after termination of treatment is currently the object of research. The majority of work to date suggests that the level of fatigue in disease-free cancer patients is correlated more strongly with psychosocial factors like activity level, sleep problems and psychological distress than to type of cancer or type and extent of cancer treatment [7,16-18].

The common regimen of CRF focuses on single interventions such as treatment of anaemia [15,19,20] – which actually is necessary if haemoglobin levels are low – or on increasing physical activity [21-25]. In many cases, though, this is not sufficient because the multidimensional character of CRF, and especially the psychosocial components are not addressed adequately. There is evidence that behavioural changes combined with an increase of the level of physical activity and the restructuring of daily routine as well as personal consultation result in a sustainable reduction of fatigue [1,3,12,13,26-31].

Our study, therefore, has aims on different levels: to create and test a self-management program which empowers disease-free cancer patients to cope with fatigue and to achieve an improvement in the outpatient care of cancer. In addition, the interaction between depression, anxiety and fatigue will be investigated.

Our predictions are:

1. Participation in the self-management program FIBS (Fatigue individuell bewältigen – ein Selbstmanagementprogramm [Coping with fatigue individually – a self-management-program]) significantly decreases the level of fatigue in disease-free cancer patients.

2. Participation in the self-management program FIBS increases the quality of life in disease-free cancer patients.

3. FIBS has a positive impact on participants' levels of anxiety and depression.

## Methods/design

### Development of the self-management program

To define the contents of the intervention an intensive literature review was conducted. The following were identified as essential subjects for the curriculum:

• medical background and causes of CRF

• physical activity and moderate exercise

• restructuring daily schedules

• energy conservation

• stress-management and relaxation strategies

• coping with negative emotions

• integrating the new knowledge into everyday life.

The program aims at impacting on health-related self-efficacy by the training of problem solving, goal setting, and cognitive techniques as knowledge transfer hasn't proved sufficient to achieve changes in behaviour. According to this we developed a curriculum in which detailed information is provided for every module concerning objectives, background, methods and materials. The program will be administered by qualified nurses to groups of eight participants. It includes six weekly sessions à 90 minutes each dealing with one of the topics listed above.

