#### Randomization

Participants are continually randomized to the self-management program or a waiting control group. Members of the waiting group receive the intervention after the intervention group has completed their follow-ups, which will be about six months after inclusion in the study. The allocation to each group will be based on a random list with balanced bloc randomization. The randomization will take place each time 16 study participants are eligible. In terms of concealment, patients will be informed of their assignment by phone.

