#### Sample size considerations

In terms of detecting a difference in FAQ scorings of 4 points with a median of 15 (alpha = 0.05; beta = 0.2) and 25% estimated rate of drop-outs, 300 patients (150 in each group) have to be recruited; therefore, about 19 randomization processes, as described above, have to be carried out over the entire term in order to assemble groups of 8 participants.

The effect size d was calculated as a result of inconsistent presumptions regarding the other outcomes describing the expected effects and standard deviations. If 300 patients are included, a small to moderate effect size of 0.35 can be detected in a two-tailed test setting alpha = 0.05 and beta = 0.2, which is assumed to be satisfactory.

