#### Data analysis

Data analysis will be carried out according to an analysis protocol following the "intention to treat principle." The primary analysis will be a comparison of the levels of fatigue in the intervention and the control groups and their changes over the course of time. Logistic regression models and variance analyses will be used to determine the impact/effect modification of secondary outcomes and to control for possible differences between the groups. All significance tests will be two-tailed and chosen allowing for scale levels.

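### Should-fix: the program is given in nurse-led groups of eight in one arm only, but the sample size makes no allowance for within-group correlation and the analysis outline names no training-group term

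*Protocol article*

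**What the plan says.** Under Development of the self-management program, the protocol article states: "The program will be administered by qualified nurses to groups of eight participants". On the course itself: "It includes six weekly sessions", each of 90 minutes.

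Under Randomization, individuals are allocated in balanced blocks: "The randomization will take place each time 16 study participants are eligible". Controls have no group sessions before their outcomes are measured: "Members of the waiting group receive the intervention after the intervention group has completed their follow-ups".

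Under Sample size considerations, the target is "detecting a difference in FAQ scorings of 4 points with a median of 15", with alpha 0.05, beta 0.2, 25% dropout and 300 patients. A detectable d of 0.35 is also given for 300 patients, two-tailed. The training groups appear there only to count randomisation rounds: "about 19 randomization processes, as described above, have to be carried out over the entire term in order to assemble groups of 8 participants". No ICC or design effect is stated.

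Under Data analysis, the primary analysis is "a comparison of the levels of fatigue in the intervention and the control groups and their changes over the course of time". Variance analyses and logistic regression are named for secondary outcomes and for group differences. No term for training group or nurse is mentioned. The section refers to a separate analysis protocol, which is not shown.

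**The concern.** This is a partially nested design. Before each post-baseline measurement, an intervention patient has spent six sessions with one tutor and up to seven peers, and a control patient has not. The content (goal setting, problem solving, coping with negative emotions) and the self-rated outcomes make some correlation within a training group plausible, though not certain.

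If that correlation is positive, the mean of the intervention arm varies more than independent observations would suggest. Two things follow. The planned power is somewhat lower than stated. And a comparison that ignores the training group has too small a standard error, so its nominal 5% test rejects too often. The second matters for the first prediction in the Background, that the program significantly reduces fatigue.

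**Working it through.** **Inputs from the protocol article.** Groups of 8; 300/16 = 18.75, so about 19 batches and about 19 intervention groups; 150 per arm; 25% dropout, which leaves 225 patients, or 112.5 per arm, and on average 8 × 0.75 = 6 per group; d = 0.35; two-sided alpha 0.05; power 80%.

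**Assumption.** The ICC is not in the documents. I use 0.02 to 0.10.

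**Step 1: the plan's own figure.** For independent observations, n per arm = 2(1.960 + 0.842)²/0.35² = 128.1, so 129 per arm and 258 evaluable patients. With 25% dropout, 258/0.75 = 344. Neither is 300.
- 300 analysed: power at d = 0.35 is 85.8% and the detectable d is 0.323.
- 225 analysed: power is 74.7% and the detectable d is 0.374.
- A rank test at its minimum relative efficiency, with no dropout, needs 129/0.864 = 149.3 per arm. This gives about 300, but the article does not state it.

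No route tried that reaches 300 contains a design effect. The 4-point figure cannot be checked, because no standard deviation is given.

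**Step 2: correlation in the intervention arm only.** With m analysed per group:
- design effect DE = 1 + (m − 1) × ICC
- variance of the standardised difference = (1 + DE)/n, with n per arm
- power = Φ(0.35/SE − 1.96)
- r = true SE/naive SE = √((1 + DE)/2)
- type I error when groups are ignored = 2 × [1 − Φ(1.96/r)]
- detectable d = 2.802 × SE

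Worked case, ICC 0.05, m = 6, n = 112.5: DE = 1.25; variance = 2.25/112.5 = 0.0200; SE = 0.1414; power = Φ(2.475 − 1.960) = 69.7%; r = 1.061; type I error = 6.5%; detectable d = 0.396.

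| Analysed | m | ICC | DE | Power at d = 0.35 | Type I error, groups ignored | Detectable d |
|---|---|---|---|---|---|---|
| 225 | any | 0 | 1.00 | 74.7% | 5.0% | 0.374 |
| 225 | 6 | 0.02 | 1.10 | 72.6% | 5.6% | 0.383 |
| 225 | 6 | 0.05 | 1.25 | 69.7% | 6.5% | 0.396 |
| 225 | 6 | 0.10 | 1.50 | 65.1% | 8.0% | 0.418 |
| 225 | 8 | 0.02 | 1.14 | 71.8% | 5.8% | 0.386 |
| 225 | 8 | 0.05 | 1.35 | 67.8% | 7.1% | 0.405 |
| 225 | 8 | 0.10 | 1.70 | 61.8% | 9.2% | 0.434 |
| 300 | any | 0 | 1.00 | 85.8% | 5.0% | 0.323 |
| 300 | 8 | 0.02 | 1.14 | 83.4% | 5.8% | 0.335 |
| 300 | 8 | 0.05 | 1.35 | 79.9% | 7.1% | 0.351 |
| 300 | 8 | 0.10 | 1.70 | 74.2% | 9.2% | 0.376 |

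With 225 analysed, m = 6 is the natural case if dropout is spread over groups; m = 8 is the upper bound, in which whole groups are lost. With all 300 analysed the groups are full, so m = 8 applies (m = 6 would give 84.1% at ICC 0.02). Simulation of 19 groups with a t-test that ignores them agrees with the type I error column to within about half a percentage point.

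**Step 3: the batch of 16.** Each batch contributes to both arms, so a shared calendar effect cancels in the treatment contrast. Assume a batch ICC of 0.05, no training-group correlation and total variance 1. The true variance is then (0.95 + 0.95)/n against a naive 2/n; r = √(1.90/2) = 0.975 and the type I error is 4.4%. With a training-group ICC of 0.05 as well and m = 8, the variance is (0.95 + 0.90 + 8 × 0.05)/n = 2.25/n, and the type I error is 6.5% instead of 7.1%. Leaving the batch out is conservative if anything.

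**The case against.** **The analysis is not fully described.** The article is a condensed text that defers to an unseen analysis protocol. Its primary test is unnamed, and variance analyses can include nested or mixed models. This stands. A reader might infer that the plan treats participants as independent and so inflates the error of its primary test; the documents do not support that. They support only that the outline names no training-group term. The sample size differs: its inputs are set out, and clustering is not among them.

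**The ICC is unknown.** A reader might conclude that the confidence intervals will be too narrow. That needs a positive ICC, which the documents do not give. At ICC 0.02 with 6 per group, power falls by only about 2 points and the type I error is 5.6%. Further, because individuals are randomised, a program and group setting that affect nobody would induce no correlation. Inflation of the type I error needs groups whose effects differ but average to zero.

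**Power depends on how the sample size paragraph is read.** If d = 0.35 refers to 300 analysed patients, the stated 80% survives an ICC up to about 0.05 (79.9%). If it refers to 225, power is already 74.7% before any clustering. So it would be wrong to attribute the whole gap from 80% to the training groups. At ICC 0.05 with 6 per group, their share is 74.7 − 69.7 = 5.0 points.

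**Ignoring the batch of 16 is not an error-inflating fault.** This stands, as step 3 shows.

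**Blinding.** The Blinding section keeps data entry and analysis blind to allocation. A group code held only by intervention patients would reveal the arm. This stands and shapes the fix; it does not remove the need for it.

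**Conclusion.** The point holds as a should-fix, not a must-fix. The design described is partially nested, the published sample size makes no allowance for it, and the analysis outline does not mention it.

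For an assumed ICC of 0.02 to 0.10 and 6 to 8 analysed per group, the type I error of a test that ignores groups is about 5.6% to 9.2%. Power at d = 0.35 falls from 74.7% to between 72.6% and 61.8% with 225 analysed, and from 85.8% to between 83.4% and 74.2% with 300. The lower end is minor and the upper end material. Nothing in the documents says where the trial lies, so the plan should state its own assumption.

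These figures cover the training group only. If one nurse leads several groups, correlation by tutor could add to them; the number of nurses is not given. Baseline adjustment is also left out, and would improve the detectable effect.

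**What to change.** 1. Record the assigned training group and the tutor for every intervention patient. Both are hard to reconstruct later.
2. Fit the primary model with a random training-group effect in the intervention arm only, treating controls as single observations, and use small-sample degrees of freedom (Satterthwaite or Kenward-Roger), since there are only about 19 groups. If the analysis protocol already does this, one sentence saying so is enough. The randomisation batch may be added for precision, but this is optional.
3. Restate the detectable effect with an ICC and a range, before baseline adjustment. For example, with 225 analysed and 6 per group: d of about 0.38, 0.40 and 0.42 at ICC 0.02, 0.05 and 0.10.
4. To respect the Blinding section, keep group and tutor codes in a separate file until the model is fixed, or give both arms the same coded batch number. Each batch of 16 supplies one group of eight, so batch and arm together identify the training group once the arm is unmasked.

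Cost: two recorded variables, one model term, a step in data handling to protect blinding, and a rewritten sentence in the sample size section. The downside is slightly wider confidence intervals and a less favourable stated detectable effect. Recruitment need not change.

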### Formative evaluation

The curriculum was reviewed and validated by an expert group of oncologists, psycho-oncologists, nurses, social workers, physical therapists, health scientists, and patients. The tutors were trained with these results. The preliminary modules were tested with a small number of patients and discussed regarding feasibility, acceptance and improvements. After revision by the expert group and the research team, the program was implemented.

### Summative evaluation

#### Design and setting

A randomized controlled trial with intervention and a control condition will be applied to evaluate the efficacy of our self-management program to reduce the level of fatigue in disease-free cancer patients. The study is conducted at the information centres for cancer in Bremen, Germany. A summary of trial design is given in figure 1.

**Figure 1 F1:**
[figure not shown]
Summary of trial design.

#### Identification of eligible patients/Inclusion and exclusion criteria

The recruitment of the patients will be carried out by oncologists in Bremen. The practices are informed about our study through participation in the expert group as well as through publications in relevant medical journals and personal information from a member of the research team. Criteria for inclusion in the study are: Patients must be over18 years of age and diagnosed with malignant tumours. They should have finished active treatment be in a stable condition with an ECOG performance status [32] of 0–2. Their level of fatigue should be rated as moderate (4–6) or severe (7–10) on a scale from 0–10. Formally, exclusion criteria are a life expectancy less than 12 months, profound brain tumours or metastases, cognitive disorders or severe psychiatric conditions.

Eligible patients will be informed of the ongoing study and asked by their oncologists to participate. They will be invited to a briefing in which they will be informed in detail about objectives and study procedures. Subsequently they will be asked to give their written informed consent.

#### Randomization

Participants are continually randomized to the self-management program or a waiting control group. Members of the waiting group receive the intervention after the intervention group has completed their follow-ups, which will be about six months after inclusion in the study. The allocation to each group will be based on a random list with balanced bloc randomization. The randomization will take place each time 16 study participants are eligible. In terms of concealment, patients will be informed of their assignment by phone.

#### Blinding

As consequence of the design with intervention compared to no intervention blinding of the participants is futile. But to avoid any bias, data entry and analysis will be performed by neutral researchers who are blinded to group allocation.

#### Data Collection and Outcome measures

Data will be collected three times by self-rated measures: Baseline data will be collected before patients are randomized to one group. The second measurement will take place each time after an intervention has taken place for the intervention and its associated control group. A follow-up will be carried out six months later.

Fatigue is the primary outcome measured by the Fatigue Assessment Questionnaire (FAQ) [33]. The instrument differentiates between physical, cognitive and affective fatigue and defines the level of fatigue on a scale from 0 to 60.

Secondary outcomes to test the behavioral impact of the intervention are general self-efficacy [34], self-efficacy of physical activity [35], levels of physical activity [36], and knowledge about fatigue and its therapy.

Further outcomes which are potentially related to/affected by fatigue are anxiety and depression measured by the German version of the hospital anxiety and depression scale (HADS) [38] and quality of life by the EORTC QLQ-C30 [39].

To control for differences between the groups and possible confounders, several sociodemographic variables and medical background information are also recorded.

Outcomes are measured at three different points in time: before randomization; after completion of the program, which is about six weeks later; and after a follow-up at six months.

#### Sample size considerations

In terms of detecting a difference in FAQ scorings of 4 points with a median of 15 (alpha = 0.05; beta = 0.2) and 25% estimated rate of drop-outs, 300 patients (150 in each group) have to be recruited; therefore, about 19 randomization processes, as described above, have to be carried out over the entire term in order to assemble groups of 8 participants.

The effect size d was calculated as a result of inconsistent presumptions regarding the other outcomes describing the expected effects and standard deviations. If 300 patients are included, a small to moderate effect size of 0.35 can be detected in a two-tailed test setting alpha = 0.05 and beta = 0.2, which is assumed to be satisfactory.

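### The detectable effect of d = 0.35 given for the outcomes other than the FAQ does not carry the plan's own 25% drop-out: with about 225 analysed it is about 0.375, or about 74% power at 0.35 (minor)

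*Protocol article*

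**What the plan says.** The section Sample size considerations in the Protocol article makes two statements.

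- **Primary outcome.** The number 300 comes from "detecting a difference in FAQ scorings of 4 points with a median of 15 (alpha = 0.05; beta = 0.2"), combined with "25% estimated rate of drop-outs, 300 patients (150 in each group) have to be recruited". Drop-out is part of this calculation. A median is given but no standard deviation.
- **Other outcomes.** A standardised effect is used because the assumptions about expected effects and standard deviations for the remaining outcomes were inconsistent. The text then says "If 300 patients are included, a small to moderate effect size of 0.35 can be detected in a two-tailed test", with the error rates given as "two-tailed test setting alpha = 0.05 and beta = 0.2", and judges this to be satisfactory. Drop-out is not mentioned here.

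The section Data analysis adds that "All significance tests will be two-tailed and chosen allowing for scale levels". It plans an intention-to-treat comparison of fatigue levels and their change over time, with variance analyses and logistic regression to control for differences between the groups.

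**The concern.** The two statements concern the same 300 patients. The first treats 300 as the number recruited, of whom a quarter are expected to be lost. The second quotes a detectable effect for 300 included, with no allowance for that loss. All outcomes are self-rated, so a patient who drops out gives no later score, and the number with data is nearer 225 than 300.

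At stake is the sensitivity claimed for the secondary and further outcomes: self-efficacy, physical activity, knowledge, anxiety, depression and quality of life. Quality of life, anxiety and depression are the subject of the second and third predictions in the Background section. A reader would take 0.35 as the effect that the trial has an 80% chance of detecting on these scales.

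**Working it through.** **Inputs.** All are from Sample size considerations: 300 recruited, 150 per arm; drop-out 25%; two-sided alpha 0.05; power 0.80; stated detectable d = 0.35. Data analysis confirms two-tailed testing. The test used below, an unadjusted two-sample comparison of means, is an assumption, because the article names no test for these outcomes.

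**Patients analysed.** 300 × (1 − 0.25) = 225, or 112.5 per arm.

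**Detectable effect, normal approximation.** d = (1.960 + 0.842) × √(2/n), with n per arm.

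- n = 150: 2.802 × 0.1155 = 0.324
- n = 112.5: 2.802 × 0.1333 = 0.374

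**Power at d = 0.35, normal approximation.** Power = Φ(0.35 × √(n/2) − 1.960).

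- n = 150: Φ(3.031 − 1.960) = Φ(1.071) = 85.8%
- n = 112.5: Φ(2.625 − 1.960) = Φ(0.665) = 74.7%

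**The same with the noncentral t distribution:**

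| Analysed | Detectable d at 80% power | Power at d = 0.35 |
|---|---|---|
| 300 (no loss) | 0.325 | 85.6% |
| 240 (if 300 was reached as 240 × 1.25) | 0.363 | 77.0% |
| 225 (25% loss) | 0.375 | 74.3% |

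The stated 0.35 is not reproduced at 300 or at 225.

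**Loss at which 0.35 would be right.** The t-test needs 129.1 per arm, rounded up to 130, so 260 in total. 1 − 260/300 = 13.3%. The article states no such rate.

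**Other routes to 0.35.**

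- A one-sided test with 225 analysed has about 83% power, but the text says two-tailed.
- A Mann-Whitney test at its minimum relative efficiency of 0.864 needs 258.2/0.864 = 299 patients for d = 0.35. This is the only variant tried that reproduces 300. It requires that nobody drops out. With 225 analysed its power is 68.0% and its detectable d is 0.404. At a relative efficiency of 0.955, power with 225 is 72.4%.

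None of the variants tried that keeps the two-tailed test and a 25% loss gives 80% power at 0.35.

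**Baseline adjustment.** Adjustment multiplies the residual SD by √(1 − ρ²), where ρ is the baseline–outcome correlation. To bring 0.375 down to 0.35: ρ = √(1 − (0.35/0.3752)²) = 0.36. The article gives no value for ρ.

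**Primary calculation.** With 225 analysed, a 4-point difference at 80% power implies SD = 4/0.375, or about 10.7. Nothing in the article contradicts that value.

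**The case against.** Four arguments can be made for the text.

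1. **The sentence is conditional and literally true.** With 300 analysed, 0.35 is detectable with room to spare (85.6% power). This fails on context: the preceding paragraph uses 300 as the number to be recruited and expects a quarter to be lost. Intention to treat does not settle the matter, since the article gives no method that would make up for missing outcomes.
2. **The analysis need not be an unadjusted t-test.** This stands in part. Variance analyses with control for group differences are planned, and a correlation of about 0.36 or more would restore 80% power at 0.35. The sample size section does not rely on this, however. The 25% is also not tied to an assessment time, so 225 analysed at both six weeks and six months is an assumption.
3. **The difference is small.** This stands. The gap is 0.025 SD, and 0.375 would still fit the article's own label of small to moderate.
4. **The d sentence does not set the sample size.** This stands, and it limits the point. A reader might infer that the trial as a whole is underpowered, or that about 347 patients should be recruited (260/0.75). That would need d = 0.35 to describe the 4-point FAQ difference, whereas the article introduces d for the other outcomes. The 300 comes from the FAQ calculation, which already includes drop-out.

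**Conclusion.** The stated detectable effect for the outcomes other than the FAQ is slightly optimistic on the plan's own drop-out rate. With about 225 analysed it is about 0.375 rather than 0.35; equivalently, power at 0.35 is about 74%, some 6 percentage points below the claim. This rests on an unadjusted two-sample t-test, 1:1 allocation and the full 25% loss applying to the assessment in question. Severity: minor.

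Two stronger readings are not supported. First, the median of 15 might be taken as proof that the primary calculation is wrong. A median does not determine a sample size, so the calculation cannot be checked as printed, but that does not make it wrong. Power figures at larger, assumed SDs would not measure an error in the plan. Second, it might be said that a null result will be misread as excluding an effect that the trial could not see. Nothing in the article proposes such a reading, and the gap is too small to carry that weight.

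**What to change.** Reword the sentence on d to say that 300 patients are randomised, about 225 are expected to be analysed, and the detectable effect for the outcomes other than the FAQ is about 0.375 at 80% power (two-sided alpha 0.05). Alternatively, keep d = 0.35 and give the power as about 74%. If baseline adjustment is counted on to regain the difference, say so and state the assumed baseline–outcome correlation; about 0.36 is enough.

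The cost is one reworded sentence and a slightly less favourable figure. The sample size, the number of randomisation rounds and the primary calculation stay as they are.
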